#### Planned interim assessments

As we have used adaptive designs, there are planned formal interim assessments for both (A) feasibility of NMP-L and (B) successful transplantation of rescued livers, with clear ‘Go’/‘No go’ decisions as detailed earlier. Ideally, recruitment (ie, transplantation) would stop while interim analyses of the primary outcome measures are performed. For (A), this could happen immediately, however for (B), this would result in a pause of over 3 months hence the pragmatic approach for such adaptive designs is to continue recruitment while they are being conducted.

To maximise patient safety, for (B) at the end of the first stage (transplantation of the first three patients), recruitment will be paused to allow the Data Monitoring Committee (DMC) to assess the initial safety data. Once all three patients are discharged, if the DMC considers the patients to be recovering well, with liver function that would be expected at this stage, recruitment can continue prior to the patients reaching the primary endpoint of 90-day survival. A follow-on report will be sent to the DMC once the third patient reaches the primary end-point. For the second stage (transplantation of 11 patients), safety data will be sent to the DMC for review after discharge of all 11 patients however recruitment need not stop at this point. A follow-on report will again be sent once the 11th patient reaches the primary end-point.

Additional DMC meetings will be conducted on request if the success criteria are not met. If recruitment is fast, prompt reviews will be necessary to ensure the use of interim decisions.

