## Statistical justification and outcome analysis

### Sample size justification

For (A) feasibility of NMP-L to rescue discarded liver grafts, it is anticipated that NMP-L will achieve a desirable organ recovery rate of at least 50%, with an undesirable rate of 30% or less as this would not be considered economically feasible. The significance level (α) is set at 0.05, corresponding to the probability of incorrectly rejecting the hypothesis given it is true (type I error), and the power is set at 0.90 (type II error rate, β=0.10), corresponding to the probability of correctly deciding the NMP-L treatment is successful given the true response rate is greater than 50%.

Using a Simon’s two-stage design^38^:

Interim assessment stage 1A of accrual: 24 marginal grafts will be perfused and assessed in the first stage. Grafts will be transplanted depending on the criteria achieved. The procedure will be considered infeasible if there are fewer than eight recovered livers. If more than eight livers are transplanted, we will proceed to Stage 2A.

Final stage 2A of accrual: Up to additional 29 marginal grafts will be perfused. We would consider the procedure feasible if there are at least 22 recovered livers out of 53 perfused livers.

For (B) for viable livers transplanted following NMP-L, a desirable 90-day patient survival rate is at least 88%, with an undesirable rate of 73% (15% lower). The mean 90-day patient survival rate for ‘standard’ liver transplants is 93%.^42^ An optimal three-stage design^39^ will be used to test the null hypothesis that the mean 90-day patient survival rate will be less than 73% (p≤0.73) versus an alternative hypothesis that the 90-day patient survival rate will be at least 88% (p≥0.88). The significance level is set at 0.20 (target α=0.2), giving a 0.2 probability to conclude that a single transplantation is viable when it truly is not viable. The power is set at 80% (target β=0.2), giving a 0.2 probability to conclude that a single transplantation is not viable when it truly is viable.

Interim assessment stage 1B: Following transplantation in three patients, the trial will stop early (concluding p≤0.73) if there are fewer than two patients achieving 90-day survival. If two or more patients reach the primary end point of 90-day survival, an additional eight transplantations will be performed.

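### The 90-day stopping counts for outcome B are not tied to the death that settles them, so recipients may be transplanted after a stage, or the trial, can no longer succeed

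*Protocol article*

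**What the plan says.** In the protocol article, *Sample size justification* gives three rules for B.

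- Stage 1B, 3 transplants: stop with fewer than 2 survivors at day 90. Otherwise, "If two or more patients reach the primary end point of 90-day survival, an additional eight transplantations will be performed".
- Stage 2B, 11 transplants: stop with 7 or fewer survivors; with 8 or more, add 11.
- Stage 3B, 22 transplants: success needs at least 18 survivors.

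*Planned interim assessments* calls these clear go/no-go decisions but does not halt accrual for them. Waiting for B is rejected because "this would result in a pause of over 3 months hence the pragmatic approach for such adaptive designs is to continue recruitment". Recruitment pauses after patient 3 until all three are discharged and the DMC is content, which may be before day 90. At 11 patients the DMC receives safety data after discharge, with no required pause, and "A follow-on report will again be sent once the 11th patient reaches the primary end-point". The section adds that "Additional DMC meetings will be conducted on request if the success criteria are not met", and asks for prompt reviews if recruitment is fast.

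Three other sections matter.

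- *Those events not being reported*: deaths within 90 days are reported within 24 hours. Entry is suspended temporarily after a recipient's death while the management group and clinical team review the cause.
- *Trial organisational structure*: two scheduled DMC meetings after the interim analyses, and a possible emergency meeting.
- *Analysis of outcome measures*: all transplantations performed enter the interim and final analyses of B.

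**The concern.** A count-based rule is often settled before the last patient reaches day 90. Under the printed bounds, failure is certain at the second death among the first 3, the fourth among the first 11, or the fifth among all 22. The article ties no action to those deaths. The formal count follows at day 90 of patient 3 or 11, and transplantation may go on meanwhile. For the fifth death there is no scheduled reading before the end.

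At stake is the exposure of recipients to discarded livers in a trial that can no longer reach its own criterion. The article presents the staged design as a patient-safety feature, so this matters more than it would for a design chosen only for efficiency. It is also not stated whether patients transplanted while a count is pending could reverse a boundary already crossed.

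**Working it through.** **Inputs from the article.** Null survival 0.73, alternative 0.88; "The significance level is set at 0.20 (target α=0.2"); power target 0.80; stages 3, 11 and 22; go at ≥2 and ≥8; success at ≥18; recruitment of 24 months (*Trial status*).

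**Assumptions not in the article.** Even average accrual, 22/24 = 0.92 transplants per month; 21 days to discharge for the stage 1 pause; deaths either early (exponential, scale 20 days, truncated at 90) or uniform over 90 days; rules acted on only at the scheduled readings.

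**Step 1: the plan's own error rates.** With X1 survivors among the first 3 and X2 among the first 11:

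P(success) = Σ over k = 8 to 11 of P(X1 ≥ 2, X2 = k) × P(Bin(11, p) ≥ 18 − k)

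| k | Joint probability at p = 0.73 | P(≥ 18 − k of 11) | Product |
|---|---|---|---|
| 8 | 0.2222 | 0.1590 | 0.0353 |
| 9 | 0.2232 | 0.3951 | 0.0882 |
| 10 | 0.1276 | 0.6570 | 0.0839 |
| 11 | 0.0314 | 0.8507 | 0.0267 |

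The sum is 0.234 (from unrounded terms). The same recursion at p = 0.88 gives 0.857. The printed rules therefore do not reproduce the targets of 0.20 and 0.80. Of the neighbouring bounds tried, only going on at ≥9 of 11, with the other bounds unchanged, meets both targets (0.1987 and 0.8033). The deciding death among the first 11 would then be the third, not the fourth.

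**Step 2: does acting at the deciding death change the error rates?** A patient-by-patient recursion that stops at the 2nd death in 3, the 4th in 11 or the 5th overall gives 0.234 and 0.857 again. The decision is already fixed and is only brought forward. With outcomes known at once, mean transplants fall from 16.21 to 14.25 at 73% and from 20.99 to 20.71 at 88%.

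**Step 3: transplants after certainty with 90-day follow-up.** Exact probabilities of failing at each stage, multiplied by the simulated mean number of later transplants (uniform to early deaths):

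| Fails at | Probability, 73% | Later transplants | Product | Probability, 88% | Later transplants | Product |
|---|---|---|---|---|---|---|
| Stage 1B | 0.179 | 1.5–2.2 | 0.27–0.39 | 0.040 | 1.5–2.1 | 0.06–0.08 |
| Stage 2B | 0.216 | 3.0–3.8 | 0.65–0.82 | 0.024 | 2.5–3.5 | 0.06–0.08 |
| Stage 3B (5th death) | 0.370 | 3.0–3.5 | 1.11–1.30 | 0.080 | 2.0–2.4 | 0.16–0.20 |
| Total | | | 2.03–2.51 | | | 0.28–0.36 |

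Across simulation runs the 73% total was 2.0 to 2.6, with at least one such transplant in about 58% to 68% of trials. The two interim bounds alone gave 0.9 to 1.2, in 31% to 36% of trials. At 88% the total was about 0.3 to 0.4, in 9% to 12% of trials.

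**Step 4: crediting the safeguards.** A suspension of 14 to 60 days after every death leaves 1.8 to 2.5 recipients and 50% to 67% of trials at 73%. If the stage 1 pause prevented all excess at that stage, the totals would be 2.03 − 0.27 = 1.76 to 2.51 − 0.39 = 2.12.

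**The case against.** The strongest reply is that the plan has real protection between the formal readings. An early second death among the first three would meet the mandatory pause, which lifts only if the DMC is satisfied. The DMC sees safety data on all 11 before day 90 of the eleventh. Entry is suspended after a death, so accrual halts at the deciding death itself, and the management group that reviews it includes the trial statisticians. The article explains openly why accrual continues. DMC triggers may also stand in the charter or the full protocol, which are not shown.

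Much of this stands, and it rules out several stronger readings.

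- A reader might infer that nothing happens until day 90, or that recipients *will* be transplanted after failure is certain. The safeguards above may intervene, so the supportable word is *may*.
- A reader might take the on-request sentence to mean that a failed criterion convenes the DMC only on request. It concerns meetings additional to the two scheduled ones.
- A reader might infer a material rise in type I error if stops are treated as advisory. The article says the trial will stop. Even if stops were ignored, P(Bin(22, 0.73) ≥ 18) = 0.252 against 0.234, a rise of 0.018.
- A reader might say patients treated during a pending count are not covered. They are included in the analyses; what is open is whether they can reverse a crossed boundary.

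The reply does not remove the gap. The stage 1 pause can end before day 90, the review at 11 need not stop recruitment, the suspension ends with the cause-of-death review whatever the cumulative count, and the emergency meeting is optional. The point does not depend on unseen detail: the article itself sets out the timing of the counts and the suspension, and leaves them unconnected.

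**Conclusion.** The point holds in a limited form. The article fixes binding counts, formally reports them to the DMC at day 90 of patients 3 and 11 while accrual may continue, and links none of its intermediate safeguards to those counts. Followed as written, the plan can lead to transplants after a stage or the whole trial can no longer succeed.

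The size is modest but not negligible if the technique performs at the undesirable rate: about 2.0 to 2.6 recipients, roughly half of them owing to the fifth-death bound rather than the interim readings. It is small at the desirable rate. These figures rest on assumed accrual and death timing. The equality of error rates with and without earlier action is exact and does not. The change is worth making because it adds protection without altering the test.

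**What to change.** 1. First reconcile the stage 2B bound with the stated alpha of 0.20, since that bound fixes which death is decisive among the first 11.
2. Link the existing suspension after a death to the B counts. When the number of 90-day deaths makes the current stage threshold or the final threshold unreachable, the suspension stays in force and the DMC is convened automatically rather than on request.
3. State that patients already transplanted at that moment are followed and reported but do not reverse a crossed boundary.

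**Cost.** Wording in the protocol and DMC charter; deaths already reach the trial team within 24 hours. Attained alpha and power do not change. When the trial fails, fewer patients contribute to the secondary outcomes, and the primary estimate is less precise and somewhat lower. With outcomes known at once and true survival of 73%, the mean observed rate falls from 0.648 under the printed rule to 0.620. The planned Wilson interval makes no allowance for stopping in either case, so the report should say so.

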#### Secondary analysis

For all secondary outcome measures, analyses will be mainly descriptive. Continuous exploratory measures will be summarised via means, medians, SD and ranges. Categorical measures will be summarised with number and proportion in each category. To model repeated measures over time (eg, QoL), a linear mixed effects model (considering subject correlation) using parametric and more flexible models may be considered. Time-to-event outcomes will be assessed using the method of Kaplan and Meier. Median survival with corresponding 95% CI will also be reported where appropriate. The assessment of graft function post-transplantation by incidence of primary non-function and early allograft dysfunction will be carried out by comparing results with a contemporary matched recipient group of patients obtained from a prospectively maintained database, with adjustment for potential confounders.

The contemporary matched recipient group will be matched using the following:Patient characteristics: age, sex, BMI, model for end-stage liver disease (MELD), UK end-stage liver disease (UKELD), aetiology;Donor liver characteristics: DCD or DBD, sex.

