### Recipient inclusion criteria

Suitable potential VITTAL graft recipients will be identified during the listing process. Patients will be told that they are potentially suitable to receive a graft from the VITTAL trial and will be given the patient information sheets to read more about the trial. If already listed, potential recipients will be identified on the list, contacted and sent the same documentation. If they wish to take part, a minimum of verbal consent will be taken. Enrolling in the trial will in no way impact on the chance of them receiving a standard ‘transplantable’ graft. Patient’s with all aetiologies of chronic liver disease will be considered for inclusion. Listed patients must meet all of the following inclusion criteria to be eligible for participation in the VITTAL trial:Adult primary liver transplant recipient;Patient listed electively for transplantation;Low to moderate transplant risk candidate, suitable for marginal graft, as assessed by the UHBFT liver transplant listing multidisciplinary team (MDT) meeting (these are usually candidates with low UKELD score, without cardiovascular comorbidities, with good functional and nutrition status, with patent portal vein and with no history of previous major upper abdominal surgery, for example, patients transplanted for liver cancer);There is no lower limit for MELD or UKELD. Upper UKELD is discussed in the exclusion criteria below.

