### Recipient exclusion criteria

Subjects who meet any of the following exclusion criteria are excluded from participating in the VITTAL trial:‘High-risk patients’ and recipients not considered suitable for a marginal graft (these are mainly patients with high UKELD score (>62 as per the NHSBT Liver Advisory Group (LAG) criteria for graft sharing in high-risk recipients in the North East of the UK with cardiovascular comorbidities or renal insufficiency, with poor nutrition and performance status or history of major upper abdominal surgery, for example, patients listed for liver retransplantation) (http://www.odt.nhs.uk, search ‘Liver Allocation Policy’);Patients with complete portal vein thrombosis diagnosed prior to the transplantation;Liver retransplantation;Patients with fulminant hepatic failure;Patients undergoing transplantation of more than one organ;Contraindication to magnetic resonance imaging (ie, pacemaker fitted).

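### The matched control pool for graft dysfunction is not limited to recipients who meet the trial's own criteria, so recipient selection confounds the comparison in an unknown net direction

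*Protocol article*

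**What the plan says.** The Secondary analysis section of the protocol article states that primary non-function and early allograft dysfunction will be assessed by "comparing results with a contemporary matched recipient group of patients obtained from a prospectively maintained database, with adjustment for potential confounders". It then introduces the match list: "The contemporary matched recipient group will be matched using the following". For recipients: "Patient characteristics: age, sex, BMI, model for end-stage liver disease (MELD), UK end-stage liver disease (UKELD), aetiology". For donors: "Donor liver characteristics: DCD or DBD, sex". No condition is set on who may enter the pool, and the confounders to be adjusted for are not named. The same section calls the secondary analyses mainly descriptive.

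Trial recipients are selected more narrowly. Recipient inclusion criteria require an adult, electively listed, primary transplant candidate who is also a "Low to moderate transplant risk candidate, suitable for marginal graft, as assessed by the UHBFT liver transplant listing multidisciplinary team (MDT) meeting". Such candidates are described as usually having a low UKELD score and being "without cardiovascular comorbidities, with good functional and nutrition status, with patent portal vein and with no history of previous major upper abdominal surgery". Recipient exclusion criteria add "Patients with complete portal vein thrombosis diagnosed prior to the transplantation", retransplantation, fulminant hepatic failure and transplantation of more than one organ, together with a high-risk group that is mainly characterised by UKELD above 62, comorbidity, poor fitness or previous surgery.

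**The concern.** A control group answers the question only if its members could have been in the trial. Here the trial arm passes through a recipient filter that the control pool, as written, does not. The article itself treats that filter as relevant to outcome: its Discussion describes giving high-risk organs to low-to-moderate-risk recipients as the safest and most successful strategy shown so far. If selection improves results, controls who did not pass it are not like-for-like.

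The stake is limited but real. Ninety-day survival is tested against fixed rates, and the other secondary outcomes are summarised without a control group. This is the one comparison in the article that sets rescued livers against contemporary recipients, so it is where a reader will look to judge whether they function as well as routinely used grafts.

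**Working it through.** The article gives no expected rate, matching ratio or power for this comparison, so there is no planned figure to reproduce. The main check is textual.

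**Recipient criteria against the match list**

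| Trial criterion | Covered by the match list? |
|---|---|
| UKELD not above 62 | Yes, through UKELD |
| No fulminant failure | Largely, through aetiology |
| No renal insufficiency | Perhaps in part, through MELD |
| Elective listing | No |
| Primary transplant, no retransplantation | No |
| Single organ | No |
| No complete portal vein thrombosis | No |
| No previous major upper abdominal surgery | No |
| Cardiovascular, functional and nutritional status; MDT judgement | No |

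**Donor side.** Only DCD/DBD and sex are matched. Under Graft inclusion criteria, trial livers were turned down by all other UK centres and carry at least one marker of marginal quality. The Discussion says high-risk livers do worse than standard grafts, most visibly in the first 90 days. This imbalance works against the trial arm.

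**Illustration of the two components.** Every input below is an assumption; none is in the article.

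- q = share of matched controls who would fail trial eligibility: 0.1 to 0.3.
- r = risk ratio for graft dysfunction, ineligible against eligible controls: 1.25 to 2.0.
- d = risk ratio for graft dysfunction from unmatched donor quality, trial grafts against control grafts: 1.0 to 2.0.
- Perfusion itself has no effect.

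Inflation of the control rate = (1 − q) + q × r:

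- q = 0.1, r = 1.25: 0.9 + 0.125 = 1.025
- q = 0.2, r = 1.5: 0.8 + 0.30 = 1.10
- q = 0.3, r = 2.0: 0.7 + 0.60 = 1.30

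Apparent risk ratio, trial against control = d ÷ inflation:

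| d | inflation 1.025 | inflation 1.10 | inflation 1.30 |
|---|---|---|---|
| 1.0 | 0.98 | 0.91 | 0.77 |
| 1.25 | 1.22 | 1.14 | 0.96 |
| 1.5 | 1.46 | 1.36 | 1.15 |
| 2.0 | 1.95 | 1.82 | 1.54 |

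The first row isolates recipient selection, and there perfused livers look better than they are. Once donor quality is allowed to differ, eight of the nine remaining cells exceed 1, so perfused livers look worse. The sign depends on inputs that the article does not supply.

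**On the absolute scale**, the recipient component is share × excess risk. If ineligible controls have a dysfunction rate 5 to 20 percentage points higher (again assumed), it runs from 0.1 × 5 = 0.5 points, through 0.2 × 10 = 2 points, to 0.3 × 20 = 6 points.

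**Precision.** With the planned 22 transplants, 5 events (an example) give 22.7%, with a Wilson 95% interval of 10.1% to 43.4%. The recipient component is small beside that.

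**The case against.** Several objections carry weight.

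- **The article is a condensed account.** A pool filter and a list of confounders may stand in the full protocol or the analysis plan, and the article nowhere says that ineligible recipients may be controls. This stands as a caution. But the article does not leave the comparator open: it fixes the source and an explicit match list, and following that text as written leaves the gap. If a filter exists elsewhere, the change reduces to stating it.
- **Matching and adjustment already help.** MELD, UKELD and aetiology cover part of the difference. The remaining adjustment is unspecified, and with about 22 treated patients few events can support a model, so it is a weak substitute for restriction.
- **The comorbidity and fitness features illustrate an MDT judgement; they are not fixed criteria.** This is correct. The point therefore rests on elective, primary and single-organ status and complete portal vein thrombosis, with previous surgery where recorded.
- **A filter cannot reproduce MDT judgement or balance donor quality.** Also correct. If donor quality dominates, removing the recipient component could even move the estimate further from no difference. That is a reason to report the residual imbalance, not to keep a removable one.

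A reader might infer that the comparison as a whole is biased in favour of perfused livers. The document does not support this, since donor quality pulls the other way. One could treat poorer donor quality as part of what is being studied, which would leave recipient selection as the confounder, but the article does not define the comparison in those terms.

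**Conclusion.** The point holds in a limited form. As written, the control pool is not restricted to recipients who meet the trial's criteria, and elective listing, primary transplant, single-organ transplant, portal vein status and previous major upper abdominal surgery are neither matched nor filtered. Recipient selection therefore confounds the comparison of primary non-function and early allograft dysfunction. Taken alone, this component tends to favour perfused livers, on the assumption that ineligible recipients have more graft dysfunction. The net direction is unknown and the size cannot be derived from the document; the ranges shown are illustrations only. Because the analysis is secondary, mainly descriptive and separate from both co-primary decisions, severity is minor: a cheap improvement.

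**What to change.** Add to the Secondary analysis section, ahead of the match list, wording such as: *Before matching, the control pool is restricted to contemporary recipients who meet those VITTAL recipient inclusion and exclusion criteria that the database records: adult, elective, primary, single-organ, no complete portal vein thrombosis, no fulminant hepatic failure or retransplantation, and no previous major upper abdominal surgery where this is recorded.* Then match as planned.

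Report the comparison as descriptive, and state that MDT judgement, functional and nutritional status and donor quality remain unmatched. Naming the adjustment variables in advance would also help.

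The cost is a filter on an existing database and a somewhat smaller control pool.
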